### Intervention and control conditions

Dyads will be randomized to the control arm and receive standard care or to the intervention arm and receive standard care plus the *Dil Mil* intervention. Standard care for DILs includes primary care and access to DV-related support services [45,46]. For MILs, we will offer a comprehensive health examination including a gynecological exam and screening for diabetes and hypertension, along with appropriate information, prescriptions, and/or referrals. We will routinely offer DV-related resources, such as information, counseling, and referrals to all participants, DILs and MILs, regardless of study arm.

The intervention, which will be implemented during the second and third trimesters of the DILs’ pregnancy, consists of 2 half-day group sessions with DILs, 5 half-day group sessions with MILs, and one joint half-day session with DILs and MILs. *Dil Mil* is delivered at the health center to small groups consisting of 12 DILs or MILs (i.e., 6 groups of 12 individuals), except for the joint session in which DILs and their MILs participate together.

The curriculum is based on participatory learning and action principles and uses stories, role-play, and discussion to enhance participants’ knowledge, skills, and social support (see [36] for details). Facilitators will encourage participants to critically analyze their relationships and to develop and implement responses appropriate to their families and communities. The group education sessions with MILs will focus on the physical and psyschosocial dimensions of growing older and the impact of life experiences including experience of DV and familial relationships on their current health status. Based on these discussions, MILs will be encouraged to reflect on the health of daughters and DILs. Thus, by beginning and grounding discussions of DV and women’s health in personal experiences and by addressing MILs’ health concerns, we expect to reduce the risks of the intervention to participating DILs.

In addition, the joint MIL-DIL session, which is the most sensitive session, will focus on the promotion of infant health, including the creation of a violence-free home environment using case studies and role plays. Activities will be conducted to promote peer support and dialogue, such as co-counseling, which aims to build peer support and empathy through dyadic peer counseling interactions within the small education groups [47]. Facilitators will be trained to handle tense situations with sensitivity and equanimity (e.g., through the development and practice of using scripts to defuse or respond to specific scenarios). Since the joint session occurs after rapport has been independently built with DILs and MILs in separate sessions, there are sufficient reiterations of the goals of the intervention and the need to respect each other’s views.

To mitigate stress and worry related to childcare and household responsibilities during the time spent on study visits, we will offer childcare at the study centers. Women will be provided information and advance notice (through appointments) regarding study visits and therefore can make childcare and other household arrangements in advance. Finally, food (a meal and snacks) will be provided when women attend the sessions.

The risk of loss of confidentiality and privacy during the group education sessions will be minimized by ensuring that all participants are cognizant of the ground rules of participation in a group exercise, including the fact that they do not have to reveal their full name, and they should not reveal personal information about others but talk in general terms. At the end of the first session when ground rules are introduced, participants will be asked to take a pledge that they will not disclose personal information about other group members to people outside the group. At the beginning and end of each session, participants will be reminded that it is essential to respect the confidentiality of other members of the group and not to discuss other group members’ personal information outside of the meeting. However, participants will be told to keep in mind that the proceedings of the discussion may not be kept confidential, although all those present are encouraged to do so. During the joint sessions, standardized scripts will be used to sensitively reiterate the need for respect for different views that may arise during discussions.

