### Randomization

Consenting dyads will be randomized as pairs on completion of the baseline assessment. Within each site, dyads will be randomized to ensure treatment balance after every 20 randomizations. The study statistician will employ a pseudo-randomizer software package to determine dyad treatment assignments and provide a series of sealed opaque randomization envelopes to study staff with one envelope per dyad. The participant IDs will be printed on the outside of the envelope, and the assigned study arm will be printed on a card contained in the envelope. A designated staff member at each center will open envelopes in sequential order of participant ID. Post randomization, the project director will ensure that the staff designated to facilitate intervention sessions do not conduct follow-up interviews or vice versa, and interviewers will not have access to information on treatment assignment.

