### Sample size and power analysis

We conducted a power analysis based on the proposed sample size of 144 dyads. Our analysis of feasibility and safety (Aim 1) will use descriptive statistics and comparisons between arms without predetermined expectations regarding statistical power. In contrast, data related to Aims 2 and 3 will be analyzed using the intention to treat ( ITT) principle [48,49]. Power calculations, performed assuming a significance level of 0.05, 90% retention, and no contamination, indicated that we have sufficient statistical power to detect changes in intermediary outcomes , that is, indicators of DILs’ and MILs’ empowerment (e.g., proportion of DILs who report that wife beating is unjustified). If 45% of DILs in the control arm report that wife beating is unjustified [27], we will be able to detect a relative risk of 1.6 with 88% power. Due to resource and time constraints of a phase 2 trial, we did not power the trial to detect a significant effect on DV. Nevertheless, we estimated power calculations for DV among DILs during the first 6 months postpartum based on the literature. Given the proposed sample size, we will be able to detect a relative risk of 0.5 with power ranging from 23% to 95% when the proportion reporting DV in the control arm ranges from 20% to 50%.

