**Outcomes**		
Domestic violence (measures of physical, sexual, and psychological acts of violence perpetrated by husbands, MILs, or other family members using an adapted Conflict Tactics Scale [54])	X	X
Perceived quality of life (WHOQOL-BREF [55])	X	X
Anxiety and depression (Kessler Psychological Distress Scale – K10)	X	X
Postnatal Depression (Edinburgh Postnatal Depression Scale [56])	X	
Maternal and Infant Health (maternal height, weight, weight gain during pregnancy, and BMI; infant weight, length, and head circumference)	X	

^a^Assessed only among control arm MILs and DILs.

Descriptive analyses will be conducted on data related to Aim 1 while data for Aims 2 and 3 will be analyzed using the intention to treat approach. Appropriate statistical techniques will be used to compare study arms on outcomes of interest (DILs’ and MILs’ empowerment, DV incidence, quality of life, anxiety and depression and maternal and infant health status) and, tailored by whether the outcome is binary, categorical, or continuous. Analytic models of intervention effect will include adjustments for individual-level demographic and background variables, such as age, education, and socioeconomic status, measured at baseline prior to randomization to examine for improved precision and to adjust for any (random) covariate imbalance across groups [57]. Longitudinal measurements of outcomes will be exploited using statistical techniques for matched or longitudinal analysis (matched pair analysis, before-after comparisons, generalized estimating equations for longitudinal models) to assess whether additional precision in efficacy estimates is possible. Finally, in the intervention group, we will explore the association between number of sessions attended by MILs and DILs and DV incidence to examine possible dose–response.

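### The stated 88% power assumes independent women, although the whole intervention arm is treated in six interacting groups of 12 and no correlation method the article names covers delivery group

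*Protocol article*

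**What the plan says.** The Randomization section allocates dyads individually: "Within each site, dyads will be randomized to ensure treatment balance after every 20 randomizations". The Intervention and control conditions section then has the intervention "delivered at the health center to small groups consisting of 12 DILs or MILs (i.e., 6 groups of 12 individuals"), apart from one joint session for DILs and MILs. Control dyads receive standard care and are not formed into groups. The groups are meant to interact: the same section describes role-play, discussion and peer co-counselling inside them.

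The Sample size and power analysis section starts from 144 dyads and gives its assumptions: "Power calculations, performed assuming a significance level of 0.05, 90% retention, and no contamination". Its worked example is "If 45% of DILs in the control arm report that wife beating is unjustified", for which "we will be able to detect a relative risk of 1.6 with 88% power".

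The Quantitative assessments and analytic plan section leaves the main between-arm technique open, to be suited to the type of outcome. It adds individual-level baseline covariates and, to gain precision, "matched pair analysis, before-after comparisons, generalized estimating equations for longitudinal models". Chi-square, t and Wilcoxon tests are mentioned for bivariable relationships, in a paragraph about work done before effects are estimated. Delivery group is not named anywhere as a source of correlation.

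**The concern.** This is a partially nested design: individual randomisation, with clusters that form after randomisation and in one arm only. Women who share a facilitator, discussions and peer counselling may end up more alike than women drawn at random. Attitudes and social support are the likeliest to show this, because the groups are designed to move them and they are Aim 2 measures. If the within-group correlation is positive, the intervention-arm mean or proportion is less precise than 72 independent women would give. Two things follow:

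- The stated power is then too high, because it makes no allowance for this.
- If the effect models also omit group, intervals are too narrow and p-values too small. The error would favour the evidence on empowerment that the Discussion lists among the criteria for a phase 3 trial.

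**Working it through.** **Inputs from the article**
- 144 dyads, 90% retention, significance level 0.05 (taken as two-sided).
- Equal allocation, inferred from the balance statement: 72 per arm, 72 × 0.9 = 64.8 evaluable.
- Control proportion 0.45; relative risk 1.6, so 0.45 × 1.6 = 0.72.
- 6 × 12 = 72, read as six DIL groups (and likewise six MIL groups) that take up the whole arm; 12 × 0.9 = 10.8 evaluable per group.

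**Assumption, not in the article:** ICC of 0.01, 0.02, 0.05 or 0.10.

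**Step 1. Reproduce the 88%.** The mean proportion is (0.45 + 0.72)/2 = 0.585.
- SE under the null = √(0.585 × 0.415 × 2/64.8) = 0.0866
- SE under the alternative = √((0.45 × 0.55 + 0.72 × 0.28)/64.8) = 0.0832
- Power = Φ((0.27 − 1.96 × 0.0866)/0.0832) = Φ(1.205) = 88.6%

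The stated figure is reached with no allowance for clustering. The match alone is not proof, since other formulas differ under independence (unpooled 90.0%, continuity-corrected 84.6%). It agrees, however, with the section's own list of assumptions, which contains no ICC.

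**Step 2. Add clustering in the intervention arm only.** Design effect DE = 1 + (10.8 − 1) × ICC. The null SE becomes √(0.585 × 0.415 × (1 + DE)/64.8) and the alternative SE √((0.2475 + 0.2016 × DE)/64.8). At ICC 0.05, DE = 1.49, the SEs are 0.0966 and 0.0920, and power = Φ(0.878) = 81.0%.

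**Step 3. Allow for only six groups.** Replace 1.96 by a t critical value on Satterthwaite degrees of freedom, with 5 df for the intervention arm.

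**Step 4. Type I error if group is ignored.** Under the null, the true SE is √((1 + DE)/2) times the naive one, so type I error = 2 × (1 − Φ(1.96/√((1 + DE)/2))).

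| ICC (assumed) | DE | Power, normal | df | Power, t | SE ratio | Type I error if group ignored |
|---|---|---|---|---|---|---|
| 0 | 1.00 | 88.6% | 22.2 | 86.2% | 1.00 | 5.0% |
| 0.01 | 1.10 | 87.1% | 20.4 | 84.2% | 1.02 | 5.6% |
| 0.02 | 1.20 | 85.6% | 19.0 | 82.2% | 1.05 | 6.1% |
| 0.05 | 1.49 | 81.0% | 15.8 | 76.0% | 1.12 | 7.9% |
| 0.10 | 1.98 | 73.6% | 12.7 | 66.0% | 1.22 | 10.8% |

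The first row separates two costs. Even at ICC 0, estimating between-group variance from six groups takes power from 88.6% to 86.2%; the rest of the fall in the t column comes from the correlation.

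A simulation (100,000 runs, beta-binomial groups, 65 per arm) gave type I errors of 5.8, 7.6 and 10.7% at ICC 0.02, 0.05 and 0.10, and 4.7% at ICC 0. Simulated values shift by up to about one point with the exact arm sizes, because the outcome is discrete, so the analytic column is the better summary.

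For scale, keeping 88.6% by normal approximation would take about 151, 158, 178 and 212 dyads at the four ICC values.

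**The case against.** A reader might infer that every planned analysis treats intervention-arm women as independent and that the standard errors will therefore be too small. The article does not support this. It leaves the main technique open, names no correlation structure for it, and condenses a fuller protocol; the statistical analysis plan is not shown and could model delivery group. The chi-square and t-tests come before effect estimation, so they are not evidence of how effects will be tested. This part of the objection stands. What can be said is narrower: the section does name methods for correlated data, and none of them covers delivery group.

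The size is also open. Nothing in the article supports a particular ICC. At 0.01 the normal-approximation loss is 1.5 points and the type I error 5.6%, both close to negligible. DILs attend only two DIL sessions and one joint session and are next interviewed at 3 and 6 months postpartum, so a large group effect by then is possible but not shown. This stands too, and every figure here is conditional for that reason.

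Finally, this is a phase 2 trial. The 88% is one illustrative outcome, the trial is expressly not powered for domestic violence, and the phase 3 criteria speak of supportive data and trends, not p-value thresholds. Clustering leaves the point estimates essentially unbiased. That lowers the priority, but it does not answer the power statement: the article itself claims sufficient power for the intermediary outcomes, and that claim rests on an unstated independence assumption its own delivery plan calls into question.

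**Conclusion.** The point holds in a limited form. The 88% is a figure for independent women, while the intervention arm is delivered in six interacting groups of 12. If the ICC lies between 0.01 and 0.10, power for the stated example is about 87% down to 74%, or about 84% down to 66% with a small-sample correction. If the eventual analysis ignored group, a nominal 5% test would have a true level of about 5.6% to 10.8%. These figures assume equal allocation, 10.8 evaluable women in each of six groups, no correlation among controls, and an ICC that the article does not supply. That the analysis will ignore group is not established. If the unseen analysis plan already models it, only the power statement needs correcting. Should be fixed; not a must-fix.

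**What to change.** 1. In Sample size and power analysis, state that the 88% is conditional on independence within delivery groups, and give power over an assumed ICC of 0.01 to 0.10, with and without the small-sample correction.
2. Record session-group membership for every intervention-arm DIL and MIL. This is easiest while sessions are running.
3. In the analytic plan, estimate Aim 2 and Aim 3 effects with a partially nested model: a group effect in the intervention arm only, each control dyad as its own cluster, and a small-sample correction (Kenward-Roger or Satterthwaite for mixed models, a bias-corrected sandwich for GEE).
4. Report the estimated ICC with its interval for phase 3 planning, noting that six groups estimate it imprecisely.

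The cost is one identifier variable and some analysis wording. The downside is wider intervals and a lower stated power, and at the upper end of the ICC range the fall is not small: 76% at 0.05 and 66% at 0.10 after correction. The sample size need not change for this reason, provided the power statement is candid.

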Safety Monitoring	Defining safety in a context of high prevalence of DV and in a population with prior history of family conflict and violence; Monitoring safety	Classification of safety-related events as “safety alerts” or “adverse events,” with alerts comprising incidents that are highly unlikely to be related to study participation and/or not considered to be severe and adverse events comprising incidents that are unexpected, temporally associated with and likely to be related to study participation and severe; Establishment of rapport with participants and creating a safe environment at the health center by offering information on DV-related resources at every visit, establishing an information desk at study health centers, and providing staff contact information; Presence of on-site counselor
Randomization	Confusion regarding or lack of understanding of randomization	Explanation of randomization in terms of a lottery; Opening of envelope with treatment assignment in front of dyad
Intervention implementation	Stress, discomfort or distress as a result of intervention participation; Loss of confidentiality in group education sessions	Establishing ground rules for group session participation including respect for each other’s views; Inclusion of activities to promote peer support and dialogue, such as co-counseling; Staff trained to handle difficult situations arising during group sessions; Counseling available on site and referral information offered; Child care and food offered; Participants and staff take a pledge of confidentiality regarding personal information shared in the group
Data collection	Stress, discomfort or distress caused by interview questions; Loss of confidentiality	Interviewers trained to conduct interviews with sensitivity and empathy; Use of statements such as, “some women can feel sad or upset by these questions—do remember that you can decide not to answer any question” repeated at strategic points of interview; Counseling available on site and referral information offered; All interviews conducted in closed room at health center; Data identified only through unique numeric identifiers

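### Participants take the confidentiality pledge only at the end of the first group session, and no pledge is described for anyone who first attends a later one

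*Protocol article*

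**What the plan says.** In Table 1 of the protocol article, the row on intervention implementation lists "Loss of confidentiality in group education sessions" among the ethical challenges. A pledge by participants and staff is one of the design responses. The table gives no timing for it.

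The timing is in the text, under Intervention and control conditions: "At the end of the first session when ground rules are introduced, participants will be asked to take a pledge". The same paragraph sets out the other safeguards:

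- **Reminders:** "At the beginning and end of each session, participants will be reminded that it is essential to respect the confidentiality of other members".
- **Ground rules:** full names are not required, and "they should not reveal personal information about others but talk in general terms".
- **Warning:** "participants will be told to keep in mind that the proceedings of the discussion may not be kept confidential".

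The intervention consists of "2 half-day group sessions with DILs, 5 half-day group sessions with MILs, and one joint half-day session with DILs and MILs". The MIL sessions cover "the impact of life experiences including experience of DV and familial relationships on their current health status". For participants in general, the article says that they will be encouraged to look critically at their relationships. Under Study setting and design, all staff sign their own confidentiality agreement.

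**The concern.** A pledge works by securing agreement before sensitive things are said. Here it is placed after the first half-day of group work. A participant who leaves that session early, or who declines to pledge when asked, has by then heard what the others said. Someone who misses the first session also misses the only pledge that the article describes.

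The setting gives this some weight. The Discussion says that dyads are randomized within selected geographic areas, and the contamination measure anticipates that control participants may know neighbors, friends or relatives in the intervention arm. The Discussion also names backlash from the husband and his family as a risk of empowering young women. Something repeated outside the group could reach those people. The stake is participant protection in the intervention arm.

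The article makes risk minimization its declared focus and chooses to state the timing of the pledge, so the stated order can fairly be questioned.

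**Working it through.** The plan gives no figure to reproduce, and no error rate, power or effect size is involved. The check sets the statements side by side and counts sessions.

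**1. Order within the first session.** The pledge falls at its end and the session lasts half a day. The first session's discussion therefore precedes the participants' pledge.

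**2. What already applies at that point.** The reminders are given at both ends of every session, and that includes the first. The first session therefore opens with an instruction to respect other members' confidentiality. The rules on names and on speaking generally, and the warning about limits, limit what is disclosed. What is absent is the participant's own promise.

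**3. When the ground rules come.** The wording of the pledge sentence allows two readings.

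- It identifies the first session as the one in which the rules are introduced. The rules may then come at its start, and nothing explains why the pledge waits.
- It places the introduction of the rules at the end of that session. This fits poorly with a reminder at its beginning.

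Either way, the text needs a clear order or a stated reason.

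**4. Share of the program that precedes the pledge.**

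- DILs: 2 separate + 1 joint = 3 sessions. The first is 1 of 2 separate sessions, or 1 of 3 in all.
- MILs: 5 separate + 1 joint = 6 sessions. The first is 1 of 5 separate sessions, or 1 of 6 in all.
- Planned number in the intervention arm, assuming equal allocation: 144 / 2 = 72 dyads, that is 72 DILs and 72 MILs. This matches the article's 6 groups of 12 (6 × 12 = 72).

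**5. Later joiners.** Under Qualitative assessments and analytic plan, the article expects to interview DILs who attended 1 or 2 of their 3 sessions and MILs who attended fewer than 5. It does not say which sessions they would miss. Simple enumeration shows that the first can be among them. Of the three ways to attend 2 of 3 sessions, one omits the first; of the three ways to attend 1 of 3, two omit it. These are possible patterns and not probabilities. The article does not say whether someone who missed the first session may join later, or whether she would then be asked to pledge.

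**6. The joint session.** The article regards this as its most sensitive session, and it follows the separate ones. For anyone who attended her first separate session, it comes after the pledge. For a later joiner, the article describes no pledge before it.

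**The case against.** The strongest reply is that the opening reminder asks for nearly the same conduct as the pledge, so moving a verbal promise by half a day may change little. The other safeguards in the paragraph also work by limiting disclosure, whenever the pledge is taken. And the detailed running order of a session belongs in a facilitator guide, which a journal article need not reproduce.

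Much of this stands, and it rules out several stronger readings:

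- A reader might infer that the first half-day runs without protection. It does not: a reminder opens it, and the rules and the warning also apply.
- A reader might infer that all participants spend that half-day discussing their own experience of violence. Grounding in personal experience is stated for the MIL sessions only. The content of the first session is not described for either group, and curriculum details are left to a cited source that is not at hand.
- A reader might infer that nobody has made a confidentiality commitment by then. Staff sign a separate agreement, so the point concerns participants only.
- A reader might infer that the order will cause additional safety events. The article gives no breach rate, and nothing in it shows how far a pledge reduces breaches beyond an opening instruction.

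The argument about level of detail has less force. The article does not leave the timing of the pledge open; it states it, and the stated timing is the weaker one. How later joiners are handled could reasonably sit in a fuller document, so that part is best taken as a request to state it.

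**Conclusion.** The point holds as a minor weakness in the order of one safeguard. As written, participants commit formally to confidentiality only after the first half-day session, which is 1 of 3 sessions for DILs and 1 of 6 for MILs. No pledge is described for someone who first attends later. The gap is in the formal commitment; other protections apply from the start of the first session.

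The conclusion takes the article's statement of the timing at face value. The part on later joiners also assumes that a participant who misses the first session may attend a later one, which the article neither states nor excludes. No frequency of breaches or of resulting safety events can be put on the point. It has no bearing on sample size, power, error rates or the analysis.

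**What to change.** State under Intervention and control conditions that the ground rules are introduced and the participants' pledge is taken at the start of the first session, before any group discussion. Add that anyone who first attends a later session, including the joint one, pledges before joining. Keep the opening and closing reminders, the ground rules and the warning as they are. If there is a reason for taking the pledge at the end, state it.

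The cost is a few minutes moved from the end of the first session to its start, a short step for later joiners, and one or two sentences of text. Sample size, assessments and analysis are unchanged.
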